## Methods

### Rationale for the study

Currently in India, some of the state governments have decided to conduct the community-based SAM treatment programme, hereinafter called CSAM, using a variety of locally produced nutrient dense food supplements, which has different energy density and nutrient composition. Locally produced nutrient dense food supplements have been chosen by state governments considering factors such as cost, availability and ease of programming. Equally, the CSAM protocol to be used in each state’s CSAM program varies. Little is known about the effectiveness and quality of recovery of children using these locally produced nutrient dense food supplements to be used under these programmes. Therefore, we propose to assess and compare the effectiveness of these programmes at two levels across five states. First, at the programme level through an assessment of programme outcomes in terms of cure rate, weight gain, relapse and mortality, and second, at the level of the individual child by assessing changes in body composition of the child over the course of treatment. This study also meets the recommendations of the WHO expert group meeting, which agreed that the demonstration of the effectiveness of a food for the treatment of acute malnutrition should not be based solely on anthropometric parameters [24].

There is a need to understand the extent to which recovery as per anthropometric and body composition parameters is achieved in each state compared to the state with no CSAM intervention (comparison state). The policy implications of the proposed study are significant in that they will provide evidence on performance of locally produced nutrient dense food supplements and currently implemented CSAM protocols in different states which will aid states in their efforts to strengthen their existing CSAM protocols and alternative food supplements.

### Intervention strategy

In general, the State Governments of Telangana, Madhya Pradesh, Odisha and Chhattisgarh will implement community-based management of SAM (CSAM) programme adapted from the WHO guidelines, in addition to the existing government nutrition promotion interventions. The approach will incorporate active and/or passive case-finding and screening for severe wasting by government frontline nutrition and health workers. For uniformity, children with WHZ < -3 will be categorized as experiencing SAM. SAM children will further undergo medical examinations and appetite test to identify complicated and uncomplicated cases. All complicated cases will be referred to the nearest nutritional rehabilitation centres (NRCs) for in-patient management. All uncomplicated cases will be enrolled in the CSAM programme for their community-based management in *anganwadi centres*. While the program’s primary focus is on treatment of children who are severely wasted, key activities also include regular follow up of all enrolled children at the *anganwadi centers*, counseling of caregivers on infant and young child feeding (IYCF), safe water, sanitation and hygiene practices, family planning and child care practices, promotion of vaccinations, appropriate referrals of sick children to NRCs or public health facilities and post discharge follow up. SAM children enrolled in the programme will also be given locally produced nutrient dense food supplements, antibiotics, anthelminthic and micronutrient supplements. Key aspects of the state specific CSAM programme are presented in Table 1. Detailed description of the state specific CSAM protocols and nutritional content of each locally produced nutrient dense food supplement is provided in Additional file 1. In the comparison area, where no CSAM intervention is being implemented, SAM children identified and enrolled in the study will receive the existing government nutrition promotion interventions. The existing program includes provision of double quantity of Take Home Ration (THR)^1^ for severely underweight children (which covers most of SAM children) and identification and referral of SAM children to Malnutrition Treatment Centres (MTCs).

**Table 1 Tab1:** Key aspects of the CSAM protocol that vary per state assessed

States	Screening & Identification	Admission criteria	Maximum treatment duration	Discharge criteria	Nutrient dense food	Post-discharge Follow up
Telangana	Active screening- once in every quarter Passive screening on all MCH contacts	SAM identification by WHZ < -3SD	16 weeks	WHZ ≥ -2SD	Balamrutam+ under ICDS provision (composition- whole wheat, Bengal gram, roasted groundnut, Jaggery, vegetable oil and added vitamin & minerals) *477 Kcal and 11 g protein per 100 g*	Monthly follow up for 6 months
Madhya Pradesh	Active screening- once in every month Passive screening on VHSND/Health Sub-centre& all MCH contacts	SAM identification by WHZ < -3SD	12 weeks	WHZ ≥ −2SD	Take Home Ration (THR) under ICDS provision by MP Agro. State THR is a mix of cereals, pulses, oil, sugar, milk powder and soya bean. *440 Kcal and 17 g protein per 100 g*	Monthly follow up for 3 months
Chhattisgarh	Active screening- once in every quarter Passive screening on VHSND/Health Sub-centre& all MCH contacts	SAM identification by WHZ < -3SD	16 weeks	WHZ ≥ -2SD	ICDS based modified THR (wheat, soybean, chickpea, sugar, vegetable oil, groundnut, finger millet). *410 Kcal and 12.75 g protein per 100 g*	1st, 3^rd^and 6th month
Odisha	Active screening- once in every quarter Passive screening on VHSND/Health Sub-centre& all MCH contacts	SAM identification by WHZ < -3SD	16 weeks	WHZ ≥ -2SD	Augmented ICDS THR (additional oil, groundnut and whole milk powder). *462 Kcal and 16 g protein per 100 g* 1 egg daily in addition to THR	1st, 3rd and 6th month

### Study aim

We aim to evaluate the effectiveness of different state specific CSAM interventions to assess their impact on anthropometry and body composition among SAM children.

### Research questions

#### Primary research question

What is the effectiveness of the CSAM programmes in four states compared to the comparison/control state among children aged 6–59 months with uncomplicated SAM in rural India?

#### Secondary research questions

Do state specific CSAM programmes help recovery of a SAM child, as defined by body composition parameters such as fat mass by skinfold thickness and fat free mass, body water by BIA, in each of the four intervention states?What is the relationship between anthropometry and body composition measures in a child suffering from SAM, in each of the five states?Do state specific CSAM programme provide better outcomes in terms of recovery, defaulting, death, length of stay and average weekly weight gain, compared to existing evidence from India?Which of the CSAM programme provides best rate of recovery 6 months after exit from the programme, defined by the relapse and mortality rates?

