### Sample size

The primary outcome of the study is cure rate at 12 weeks (in Chhattisgarh) or 16 weeks (in Telangana, Madhya Pradesh and Odisha) compared to the comparison area. Evidence on CMAM interventions in India testing its efficacy have shown cure rates ranging from 46.7 to 57.4% [19–23]. Another study from India found cure rate among 25–30% children with minimal community based interventions [26]. Hence for the sample size calculation, we therefore chose the expected cure rate with the proposed CSAM interventions of 50% and expected cure rate with existing government nutritional interventions of 25% to estimate the effect size of 25% (50–25%). The sample in each state will comprise of an equal proportion of children from the two age groups (6–23 months and 24–59 months). Using the significance level of 5%, with 80% power to detect the effect size of 25%, a design effect of 1.5 and accounting for 20% attrition due to loss of follow up and mortality, the sample size calculated for each age group of children is 100. Hence, the proposed sample size for the two age-groups of children in each state is 200 children. In total, the study will enroll 1000 children in all the five study states.

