Also, during admission and at discharge, the Field Investigator will administer the questionnaire for capturing child details and incidences of morbidity. Additionally, during admission, data on availability of drinking and sanitation facilities and other household level socio-economic information will be collected. Also,24-h dietary recall, food frequency and food consumption questionnaires will be administered to these children on admission, at sixth week and at discharge to study food consumed by the children, food frequency and compliance of locally produced nutrient dense food supplements provided to the children as part of the intervention. Futhermore, we will also ascertain cause of death of any enrolled child died during the study period.

Besides, first 100 enrolled children in that state who qualifies for body composition measurement i.e. weight on admission > 5 kg, will also be measured for body composition parameters using BIA machine (InBody S10) on admission and at discharge.

Post discharge, the children will be followed up on a monthly basis for anthropometry until 6 months by the field investigators. Additionally, skinfold thickness and body composition assessment of all children will also be repeated at sixth month post discharge. A detailed description of data collection process is shown in Table 2.

**Table 2 Tab2:** Overview of all measurements that will be taken from children

Parameters	Method	Admission/ Baseline	6th Week	12th/16thweek/Exit/Discharge	Post-discharge Follow up^b^
All children enrolled:					
Child details, and history of illness	Questionnaire	**✓**		**✓**	
Drinking water and sanitation facilities and other household socio-economic status		**✓**			
Weight, Recumbent length/ Height,	Digital weighing machine, Infantometer/ Stadiometer	**✓**	**✓**	**✓**	✓
Skinfold Thickness (triceps & subscapular skinfold)	Holtain Skinfold Caliper	**✓**	**✓**	**✓**	✓^c^
Dietary assessment (24-h dietary recall & food frequency) and Consumption of locally produced nutrient dense food	Observation and questionnaire	**✓**^**a**^	**✓**	**✓**	
Body composition; For enrolled sub-sample of children (weight > 5 kg)					
Body fat mass	BIA machine	✓		✓	
Body lean mass					✓^c^

^a^At baseline only the 24-h dietary recall & food frequency assessment will be done

^b^Post discharge, all children will be prospectively followed up for anthropometric measurements on a monthly basis till 6 months by the field investigators

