### Data analysis

Final analysis will include all children enrolled in the study. Appropriate quantitative analyses will be used including descriptive statistics (proportion, percentage, mean or median), comparison of difference in proportion for binary outcome using Pearson chi-square and comparison of average change for continuous variable using t-tests. Recovery will be compared for effectiveness of state specific CSAM protocols and locally produced nutrient dense food supplements in four intervention states in comparison to the comparison state. Cox regression method will also be used for this analysis by defining recovery as event, as it can utilize the entire sample size including defaulters or loss to follow up. Other parameters including skinfold, defaulting, death, length of stay, average weekly weight gain and height gain will also be compared between the intervention states and the control state. Subgroup analysis will be done for comparing recovery among children aged 6–23 months and 24–59 months between intervention states and control state. For the sub-sample of body composition, change in fat mass, fat free mass and body water will be compared between the four intervention states and the comparison state. A linear mixed model will be developed for different outcomes (recovery, weight gain, and body composition parameters) adjusting for various random and fixed effects across all sites adjusted for differences at baseline.

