### Cost effectiveness analysis

We will conduct cost and cost-effectiveness analyses to guide policy decisions and inform any subsequent scale up. We will estimate the total and incremental costs of the CSAM intervention in each of the four intervention study states from the provider’s perspective. The costs of delivering the CSAM interventions both at the community and the facility levels will be collected retrospectively from the accounts of government and other partnering institutions, using a standardised data capture tool designed for this purpose in Excel. This will also be combined with key informant interviews and available financial data on the average unit cost of delivering those services. Time use study will be conducted with frontline workers and other key implementers to value their time spent in the CSAM intervention. Cost of any donated resource to the CSAM intervention will also be included in the analysis. All costs will be adjusted for inflation using the Indian Consumer Price Index (CPI) and will be presented in Indian Rupees and 2021 International Dollars. Incremental cost-effectiveness will be measured in relation to the status quo alternative i.e. doing nothing in addition to the current ongoing activities as part of government nutrition promotion initiatives. Incremental cost-effectiveness ratios (ICERs) will be calculated for the primary outcome measures (i.e. SAM cases treated and cured/recovered) and selected secondary outcome measures such as cases of child mortality averted, life-years saved and disability adjusted life years (DALYs) averted. Sensitivity analyses will be carried out to assess the robustness of results.

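### Death is compared over observation windows that end at, or run from, programme exit, so faster cure or a shorter treatment cap lowers a crude death proportion even when death hazards are equal

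*Protocol article*

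**What the plan says.** Everything is in the Protocol article.

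- **Exit.** In Table 1 all four CSAM states discharge at WHZ ≥ -2, with a maximum treatment duration of 12 weeks in one state and 16 weeks in three.
- **Follow-up clock.** The Data collection section counts from discharge: "Post discharge, the children will be followed up on a monthly basis for anthropometry until 6 months by the field investigators". Table 2 has a single column for the 12th/16th-week, exit or discharge visit, covering all enrolled children.
- **Death against control.** The Data analysis section states: "Other parameters including skinfold, defaulting, death, length of stay, average weekly weight gain and height gain will also be compared between the intervention states". The sentence then names the control state as comparator. The section names Pearson chi-square for binary outcomes, Cox regression with recovery as the event, and a mixed model for recovery, weight gain and body composition. No time-based method is named for death.
- **Death between programmes.** The last secondary question asks which CSAM programme has the best "rate of recovery 6 months after exit from the programme, defined by the relapse and mortality rates".
- **Onward use.** The Cost effectiveness analysis section plans ratios for "selected secondary outcome measures such as cases of child mortality averted, life-years saved", and for DALYs averted.

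**The concern.** A death can be counted only while a child is under observation. Here the end of observation is set by the primary outcome: a child cured in week 5 leaves the treatment phase in week 5 and completes its 6 months correspondingly early. The study expects cure to differ between arms, so it also expects time at risk to differ. A chi-square comparison of the proportion who died treats the windows as equal. If death hazards are the same and cure is faster under CSAM, the crude proportion leans towards CSAM.

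The same mechanism acts between CSAM programmes with different maximum durations, which is the comparison that the last secondary question makes.

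At stake is a secondary outcome. A mortality difference that feeds a cost-effectiveness ratio is used as a point estimate, however, with no significance test to screen out a spurious fraction of a death.

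**Working it through.** **1. The plan's own figure.** The article gives no mortality figure; the only calculation to reproduce is the sample size. Inputs are an "expected cure rate with the proposed CSAM interventions of 50"%, an "expected cure rate with existing government nutritional interventions of 25"%, 5% significance (two-sided assumed) and 80% power, with "a design effect of 1.5 and accounting for 20% attrition due to loss of follow up and mortality".

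- n = (1.96 + 0.842)² × (0.50×0.50 + 0.25×0.75) / 0.25² = 54.9
- × 1.5 = 82.4; × 1.2 = 98.9, in line with the stated 100 per age group (dividing by 0.8 instead gives 103.0)

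The cure rates used below are therefore the ones the plan is built on.

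**2. Mean time to exit.** Assume a constant cure hazard λ, with a proportion p cured by the cap T. Then λ = -ln(1 - p)/T, and mean weeks to exit = (1 - e^(-λT))/λ = p/λ.

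- p = 0.50, T = 16: λ = 0.0433, mean 11.54 weeks
- p = 0.25, T = 16: λ = 0.0180, mean 13.90 weeks
- p = 0.50, T = 12: λ = 0.0578, mean 8.66 weeks

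**3. Ratios of time at risk.** Six months is taken as 26 weeks. With equal death hazards, these approximate the ratio of expected deaths.

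| Comparison | To exit | To exit + 26 weeks |
|---|---|---|
| CSAM v control, control also exits on cure | 11.54/13.90 = 0.83 | 37.54/39.90 = 0.94 |
| CSAM v control, control stays to week 16 | 11.54/16 = 0.72 | 37.54/42 = 0.89 |
| 12-week v 16-week CSAM cap, both 50% cure | 8.66/11.54 = 0.75 | 34.66/37.54 = 0.92 |
| Both arms 25% cure, same exit rule | 1.00 | 1.00 |
| Both arms 25% cure, only control stays to week 16 | 13.90/16 = 0.87 | 39.90/42 = 0.95 |
| Any, counted from enrolment to week 26 | – | 26/26 = 1.00 |

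**4. Sensitivity.** With cure times uniform among the cured, the first two rows become 0.86 and 0.75 to exit, and 0.95 and 0.90 to exit + 26 weeks. With a death hazard three times higher in the first 16 weeks, they stay at 0.83 and 0.72 to exit but move to 0.97 and 0.94 to exit + 26 weeks.

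**5. In deaths.** The article gives no mortality level, so 1%, 3% and 5% over 42 weeks are assumed. For total mortality m, h = -ln(1 - m)/42, and expected deaths in 200 children = 200 × (1 - e^(-h × weeks)). The ranges cover the two control exit rules.

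| Assumed m | To exit, CSAM v control | To exit + 26 weeks, CSAM v control |
|---|---|---|
| 1% | 0.55 v 0.66–0.76 | 1.79 v 1.90–2.00 |
| 3% | 1.67 v 2.01–2.31 | 5.37 v 5.70–6.00 |
| 5% | 2.80 v 3.37–3.87 | 8.96 v 9.51–10.00 |

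At 3% the spurious shortfall is 0.33 to 0.64 deaths per 200; at 5% it reaches about 1.1. By a normal approximation, rough at such counts, the chance of a significant crude result favouring CSAM is about 3% to 6%, against a nominal 2.5%.

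**The case against.** The strongest reply is that the article leaves the mortality window open and does not fix a wrong one. The Data analysis sentence on death gives no time limit, cause of death is to be ascertained for any enrolled child who dies during the study, and the mortality rates named as an outcome might be meant per person-time. Such detail often sits in an analysis plan. This stands in part: the article does not say that deaths against control are counted only to exit. But it is not simply silent. It runs follow-up from discharge, defines the between-programme mortality comparison from exit, names chi-square for binary outcomes and gives time-to-event analysis to recovery alone.

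Three stronger readings are tempting, and the documents do not support them:

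- **That control children have no discharge and are always observed longer.** No control exit rule is stated, and Table 2 and the abstract apply discharge and post-discharge visits to all participants. Hence the range, not the 28% alone.
- **That CSAM would show fewer deaths with no effect at all.** With equal cure and the same exit rule the ratio is 1.00. The lean needs faster cure, a shorter cap or a fixed exit for controls only.
- **That a 12-week state is set against a 16-week control, making the gap larger still.** No control horizon is given, so that pairing is an assumption.

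It is also fair to say that the link to the cost-effectiveness analysis is a possibility: that section does not say which mortality contrast it uses.

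**Conclusion.** The point holds as a modest, systematic distortion of a secondary outcome. As written, the cure outcome helps to set how long each child is observed for death, and nothing in the stated death comparison allows for this. Given equal death hazards, the planned cure rates, a constant cure hazard and 16-week caps, CSAM children have 17% less time at risk to exit if controls also exit on cure and 28% less if controls stay to week 16. To exit plus 26 weeks the figures are 6% and 11%. Between CSAM programmes with equal 50% cure, a 12-week cap gives 25% less time to exit and 8% less to exit plus 26 weeks than a 16-week cap.

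It would rarely change a significance test, and at 3% assumed mortality it amounts to less than one death per 200 children. A reader should not infer that the trial will report a false survival benefit. The case for acting is that the direction is predictable, the cost-effectiveness ratios could take it in unfiltered, and the correction is nearly free.

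**What to change.** - **Main mortality contrast.** In Data analysis, define death from enrolment, whatever the discharge date, to one day common to all five states, and compare by Kaplan-Meier or as deaths per child-month up to that day. Week 26 from enrolment works: follow-up to 6 months after any discharge date reaches it for every child. Use the same window to rank the CSAM programmes.
- **Cost-effectiveness.** State that deaths averted, life-years and DALYs use this contrast.
- **Programme indicators.** Keep deaths before and after exit as descriptive figures, which also serve the secondary question comparing outcomes with existing Indian evidence.
- **Exit rules.** State how exit is defined for control children. Reconcile the caps: the Sample size section gives 12 weeks to Chhattisgarh and 16 to Madhya Pradesh, while Table 1 gives the reverse.

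**Cost.** Analysis wording only, with no extra visit; confirm that the date of death is recorded. The downside is that deaths after the common day leave the main mortality contrast and appear only descriptively.

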### Study design and setting

This multi centric longitudinal quasi-experimental study with a comparison area will take place in two blocks each in Gadwal (state Telengana), Hoshangabad (state Madhya Pradesh), Rajnandgaon (state Chhattisgarh), Nabrangpur (state Odisha) and Latehar (state Jharkhand) districts. More than 80% population in these districts reside in rural areas with more than one-third of the households being poor [25]. The prevalence of wasting and severe wasting among children in these districts are very high. Wasting among children under five in these districts are 18.6, 29.6, 17.2, 36.0 and 29.0% respectively and severe wasting prevalence is5.1, 10.6, 6.2, 11.6 and 10.7% respectively [4]. From each of the four intervention districts, two study Blocks will be purposively selected where either the CSAM intervention is currently being implemented or have been planned by the respective state governments. Similarly, two study Blocks from Latehar district of the state Jharkhand will be purposively selected as comparison area, where no CSAM intervention is being implemented.

The study will be led by Kalawati Saran Children’s Hospital (KSCH), New Delhi and supported by Children’s Investment Fund Foundation (CIFF) through UNICEF, India. KSCH will partner with Indian Council of Medical Research-National Institute of Nutrition (ICMR-NIN), Telangana, All India Institute of Medical Science (AIIMS) in Madhya Pradesh and Chhattisgarh, National Health Mission (NHM) of Odisha and Rajendra Institute of Medical Science (RIMS), Jharkhand, who will administer and manage the study in the respective states.

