**Methods:**

The longitudinal quasi-experimental study will be undertaken in two purposively selected blocks of one district each in the four intervention states and one comparison state. From each state, 200 SAM children identified using weight-for-length/height z-score (WHZ) < **−** 3 criteria will be enrolled in the study. Their anthropometric data and skinfold thickness will be taken on admission, at sixth week and at discharge by trained field investigators. Other child details, incidence of morbidity and socio-economic details will be collected on admission. To assess food consumption pattern including consumption of locally produced nutrient dense food supplements, dietary assessment, using 24-**h** dietary recall will be conducted on admission, at sixth week and at discharge. In addition, body composition parameters will be assessed for a sub-set of children using bio-electrical impedance analysis on admission and at discharge to analyse changes in total body water, fat-free mass, and fat mass. Post discharge, all study participants will be followed up monthly until 6 months. Atleast 10% of the sample will be checked for quality assessment.

The study’s primary outcome is cure rate defined as children attaining WHZ **≥** -2. Secondary outcomes include mean weight gain, mean length of stay, body composition parameters, relapse and mortality rates. Additionally, process evaluation and cost effectiveness analysis will be conducted.

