## Discussion

Different state governments have contextualized, designed and developed operational CSAM protocols for implementing their state specific CSAM strategies to be manageable within their existing NHM and ICDS systems. The study results will be generalisable to rural areas of India with a high burden of childhood wasting and underserved community. There are a large number of high-burden districts and Blocks in India where prevalence of SAM among children is very high. If the CSAM strategies of different states improve the study’s primary and/or secondary outcomes, the intervention strategies can be scaled up to all or parts of the high- burden districts through NHM and ICDS systems. These intervention strategies will also enable the health and ICDS systems to work in collaboration with each other at the village level through their existing frontline workers.

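### Each programme is one district of one state with a single comparison district, so programme and state effects cannot be separated and the generalisability claim is unsupported

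*Protocol article*

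**What the plan says.** The Abstract (Methods) describes "two purposively selected blocks of one district each in the four intervention states and one comparison state". Study design and setting repeats this for the programme areas ("From each of the four intervention districts, two study Blocks will be purposively selected") and for the control ("two study Blocks from Latehar district of the state Jharkhand will be purposively selected as comparison area"). The primary research question asks about the effectiveness of the programmes in four states against that one comparison state.

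Sample size assumes an "expected cure rate with the proposed CSAM interventions of 50" per cent and an "expected cure rate with existing government nutritional interventions of 25" per cent, a 5% significance level, a design effect of 1.5 and 20% attrition. It arrives at 100 children per age group per state, "with 80% power to detect the effect size of 25" points. The clustering level that the 1.5 refers to is not given.

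Data analysis compares proportions by Pearson chi-square and adds Cox regression and a linear mixed model "adjusting for various random and fixed effects across all sites adjusted for differences at baseline". The Discussion concludes: "The study results will be generalisable to rural areas of India with a high burden of childhood wasting and underserved community", and says the strategies can be scaled up if outcomes improve.

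**The concern.** With one district per programme and one control district, a difference from Latehar can come from the programme or from anything else that distinguishes the two places. The protocol itself shows that the places differ. Severe wasting is 5.1, 10.6, 6.2 and 11.6% in the four CSAM districts and 10.7% in Latehar. The managing institutions differ. Cases are found by frontline workers and rechecked in the CSAM states, but by Field Investigators in the comparison state. No pre-programme or within-state comparison is described that would separate the two sources.

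A significant difference would be read as evidence that a state's food and protocol work, and would feed the scale-up argument and the cost-effectiveness ratios. Child-level tests would also overstate the certainty, because variation between districts is shared by all children in an arm and does not shrink as children are added.

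**Working it through.** **1. The plan's own figure.** Inputs from Sample size: 50% v 25%, 5% (two-sided assumed), 80% power, design effect 1.5, 20% attrition.

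n = (0.25 + 0.1875)(1.960 + 0.842)² / 0.25² = 54.9, so 55. Then 55 × 1.5 × 1.2 = 99, against the stated 100. The figure reproduces from child-level variance and the 1.5, with no separate between-district term.

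**2. What is added.** Let τ be the SD between districts of the cure rate without CSAM. One CSAM district against one control district adds 2τ² to the variance of the difference, whatever the number of children. The documents give no value for τ. I show 3 and 5 points as assumptions, which at a 25% cure rate correspond to ICCs of 0.03²/0.1875 = 0.0048 and 0.05²/0.1875 = 0.013. The two added variances are 2 × 0.03² = 0.0018 and 2 × 0.05² = 0.0050.

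**3. Type I error if τ is ignored.** Take 25% in both arms and 80% of N evaluable. The assumed variance is V₀ = 1.5 × 0.375/(0.8N), which is 0.00703 for N = 100 and 0.00352 for N = 200. The actual error is 2[1 − Φ(1.96 √(V₀/(V₀ + 2τ²)))].

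| | SD 3 points | SD 5 points |
|---|---|---|
| Per age group (N = 100) | 8% | 13% |
| All ages (N = 200) | 11% | 21% |

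These figures credit the test with the 1.5 inflation. An ordinary Pearson chi-square applies none. With V₀ = 0.375/(0.8N) and no other clustering, the same formula gives 10% and 17% per age group, and 14% and 27% for all ages.

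**4. Power if τ were known and allowed for.** Power = Φ(0.25/SE − 1.96), with SE² = D × 0.4375/(0.8N) + 2τ². D = 1.5 treats the design effect as other clustering, with τ on top. D = 1 treats district variation as the only clustering.

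| | SD 3, D = 1.5 | SD 3, D = 1 | SD 5, D = 1.5 | SD 5, D = 1 |
|---|---|---|---|---|
| Per age group | 71% | 83% | 59% | 69% |
| All ages | 90% | 96% | 75% | 81% |

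For example, all ages at SD 5 with D = 1.5: SE² = 0.00410 + 0.0050 and SE = 0.095, so power = Φ(2.62 − 1.96) = 75%. With τ = 0 and D = 1.5, power is 79% per age group and 97% for all ages.

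**5. Can the data supply τ?** No. A single-state contrast has one district on each side, which leaves no degrees of freedom for variation between districts. Pooling the four CSAM states leaves 3 degrees of freedom, but still one control district, and the four programmes differ in product and protocol, so their spread is not purely district variation. The two blocks per district inform variation within a district only.

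**The case against.** The strongest reply is that the design is openly disclosed. The study is called quasi-experimental, block selection is called purposive, and the programmes are run by state governments, so programme and state coincide by construction. That is fair, and the design need not change. But disclosing non-randomisation does not qualify the generalisability statement. That statement is limited to high-burden, underserved rural areas and should not be read as a claim about all rural India. Even so limited, five purposively chosen districts do not support it.

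Three stronger readings are tempting, and the documents do not support them.

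- *The mixed model is unidentifiable because a CSAM effect is fitted on top of site effects.* Data analysis specifies no such model. State as the fixed exposure with random effects below it is a permitted reading, and the exact specification may sit in an analysis plan that is not shown.
- *The 1.5 cannot cover area variation because at two children per centre it would need a centre ICC of 0.5.* The protocol never says the 1.5 is for centres. Read at district level with 100 children, it implies 0.5/99 = 0.005, close to the SD 3 case. Keeping 1.5 and adding 2τ² may then count the same variance twice, which is why power is shown both ways.
- *The 80% power holds only if there is no district variation.* For all ages, power stays at or above 90% at SD 3 on either reading. The lower figures belong to the age groups, which Data analysis treats as subgroups, although the sample size was calculated for them.

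It also stands that the SDs are assumptions and that the calculation gives no credit for the planned baseline adjustment. That adjustment can remove measured differences only.

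**Conclusion.** The point holds for interpretation and precision. That programme and state cannot be separated follows from the design and needs no numerical assumption. The generalisability statement claims a property this design does not have.

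The size of the error depends on an assumed between-district SD. At 3 to 5 points, a nominal 5% test has a true error of about 8–13% per age group and 11–21% for all children in a state. The stated 80% power contains no explicit between-district term. The loss depends on how the 1.5 is read: power is about 71–83% (SD 3) and 59–69% (SD 5) per age group, and 90–96% and 75–81% for all ages. A reader should not infer that the sample size is wrong on its own terms, since it reproduces, or that the planned model cannot be fitted.

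**What to change.** 1. **Discussion.** Restrict the conclusion to the adjusted difference between each state's CSAM blocks and the Latehar blocks. State that programme and state effects cannot be separated. Drop the generalisability claim or make it conditional on that limitation.
2. **Data analysis.** Enter state once, as a five-level exposure, with a random intercept for anganwadi centre. Add a sensitivity analysis that widens each interval for an assumed between-district SD of 0 to 5 points. For all ages at the planning rates with the 1.5 retained, the half-width goes from 1.96 × √0.00410 = 12.6 points at SD 0 to 1.96 × √0.00910 = 18.7 points at SD 5.
3. **Sample size.** State the level that the design effect of 1.5 covers, and that the 80% power makes no separate allowance for variation between districts.

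The cost is wording and one sensitivity analysis, with no new sites or data. The downside is a more modest claim and wider sensitivity intervals.
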